## Methods and analysis

### Trial design and timeline

XANDTX is conceptualized as a single-centre open-label, randomized, controlled therapeutic exploratory feasibility study. Patients planned for elective periampullary tumor resection will be assessed for eligibility and eligible patients will be informed about the trial in detail. After written informed consent and in the case of intraoperative presence of a POPF high-risk constellation (soft pancreatic texture and pancreatic duct diameter ≤ 3 mm), 32 patients will be intraoperatively allocated in a 1:1 ratio to undergo either PD or TP with simultaneous IAT (Fig 1). Randomization will be performed via sealed envelopes (block randomization).

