#### Statistical methods.

The data collected within this exploratory trial will provide the basis for a subsequent confirmatory controlled study. Therefore, no formal sample size estimation was performed. Assuming an event rate of about 60 percent, a sample size of 30 patients (15 individuals per treatment group) allows for the detection of a hazard ratio of approximately 0.31 (two-sided significance level of 10%, power of 80%). Assuming a drop-out rate of 5%, 16 patients per treatment group will be included. 

The main analysis will be performed after completion of the two-year follow-up period (including data collection and cleaning) in the entire intention-to-treat population. No interim efficacy analyses are planned in this study. All analyses will be performed using SAS 9.4 or higher.

The confirmatory analysis of the primary endpoint and the analysis of the secondary endpoints will be performed according to ICH E9 [21] using the full analysis set (intention-to-treat population) and follow the intention-to-treat principle. The full analysis set will include all randomized patients.

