##### Safety analysis set

The safety analysis set includes all patients in whom the investigational therapy was used.

For long-term oncologic outcomes (survival analyses), patients lost to follow-up and patients deceased within the observation period will be censored. A per-protocol analysis is planned for sensitivity analysis.

The primary endpoint (time between surgery and day of “fit for adjuvant treatment”) is defined as the interval between day of surgery and day of oncologists decision that patient is fit to start the administration of adjuvant chemotherapy, measured in days. It will be analyzed using Kaplan-Meier estimators (with a two-sided confidence level of 90 percent). Comparison of the primary endpoint between the treatment groups will be performed using the log-rank test. In case of proportional observed hazards in the control and treatment groups, a Cox proportional-hazards model will be used to examine which covariates have an impact on the hazard ratio of the two treatments. Safety analysis will include the frequency of (serious) adverse events in the safety analysis set. Annual safety analyses will be performed in accordance with regulatory requirements. Frequencies and types of adverse events (AE, SAE) will be summarized as relative frequencies (proportions) and, if applicable, the occurrence of specific events (at the patient level) of the two groups will be compared using chi-square test. QLQ-C30/Pan26 questionnaires will be analyzed using a mixed model with the patient as a random factor analysis, including comparison of changes in quality of life over time between the two treatment groups, and respective covariates potentially impacting quality of life within each of the two treatments. Exact Chi-Square test will be used to analyze perioperative morbidity and mortality. Metabolic outcome over time will be analyzed using a mixed model with the patient as a random factor. To analyze the oncologic outcome, a Cox regression model will be used.

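### Adverse events get an ordinary chi-square test and perioperative morbidity and mortality an exact one, so the same sparse counts can give different answers (minor)

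*Protocol article*

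**What the plan says.** The paragraph on analyses under Safety analysis set in the Protocol article names two tests for patient-level proportions. Adverse events are first summarised as proportions, and then, where applicable, "the occurrence of specific events (at the patient level) of the two groups will be compared using chi-square test". Two sentences later: "Exact Chi-Square test will be used to analyze perioperative morbidity and mortality". The article gives no reason for the difference, no rule for small expected counts and no significance level for either test.

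On size, Statistical methods states that "16 patients per treatment group will be included", and Trial design and timeline gives 1:1 allocation of 32 patients. The only error level in the document, "two-sided significance level of 10%, power of 80"%, belongs to the detectable effect for the primary endpoint.

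The populations also differ. Secondary endpoints, which include perioperative morbidity and mortality, use the full analysis set of all randomized patients. Adverse events use the safety analysis set, defined as the patients in whom the investigational therapy was used.

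**The concern.** The section on reporting adverse events has all AEs and SAEs documented for both treatment methods. A perioperative complication can therefore be counted once as morbidity and once as an adverse event, and be tested differently each time. With arms this small the large-sample chi-square and its exact counterpart can give quite different p-values. Safety is a declared aim of the pilot, and its results are meant to inform a confirmatory trial. A reader comparing the two sets of results should not find that the p-value depends on which table an event was printed in.

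**Working it through.** **The plan's own figures.** The document gives no figure for these two tests. Its sample-size figures reproduce:
- 60% of 30 patients is 18 events. Schoenfeld's formula gives HR = exp(−2 × (1.645 + 0.842) / √18) = exp(−1.172) = 0.31, as stated.
- 30 / 0.95 = 31.6, rounded up to 32, or 16 per arm.

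**Inputs.** 16 v 16 comes from Statistical methods. Applying it to adverse events assumes that the safety comparison contains both arms in full. The levels 5% and 10% are also assumptions for these tests, since 10% is stated only for the primary endpoint.

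**Expected counts.** With m patients having the event out of 32, each arm expects 16 × m / 32 = m / 2. This is below 5 whenever m < 10. For in-hospital mortality at the 4.1% cited in the Discussion, 32 × 0.041 = 1.3 deaths are expected in total.

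**One table by hand, 0/16 v 4/16.**
- Ordinary (Pearson, uncorrected): χ² = 32 × (0 × 12 − 16 × 4)² / (16 × 16 × 4 × 28) = 131072 / 28672 = 4.57 on 1 df, p = 0.033.
- Exact: given 4 events in total, P(all four in one named arm) = C(16,4) / C(32,4) = 1820 / 35960 = 0.0506. Doubled for the mirror table, p = 0.101.

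**All tables.** Every one of the 17 × 17 = 289 tables was enumerated. The exact p-value is that of the Pearson statistic under the hypergeometric distribution, which here equals two-sided Fisher.

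| Counts | Ordinary p | Exact p |
|---|---|---|
| 0 v 3 | 0.069 | 0.226 |
| 0 v 4 | 0.033 | 0.101 |
| 1 v 6 | 0.033 | 0.083 |
| 2 v 7 | 0.049 | 0.113 |
| 5 v 10 | 0.077 | 0.156 |
| 5 v 11 | 0.034 | 0.076 |

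The tests disagree in 26 of 289 tables at 5% and in 28 at 10%. In each case the ordinary test is significant and the exact test is not.

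**True size, maximised over a common event rate.**

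| Arms | Test | Nominal 5% | Nominal 10% |
|---|---|---|---|
| 16 v 16 | Ordinary | 5.8% | 11.0% |
| 16 v 16 | Exact | 2.0% | 5.0% |
| 15 v 15 | Ordinary | 5.5% | 11.9% |
| 15 v 15 | Exact | 1.8% | 4.3% |
| 15 v 16 | Ordinary | 7.1% | 11.3% |
| 15 v 16 | Exact | 3.0% | 7.1% |

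For rare events the ordinary test is itself below nominal: at a 5% event rate and 16 v 16 its size is 0.6% and 3.8%. Its marked excess appears only conditionally on certain small totals: 10.1% at nominal 5% given 4 events, and 22.6% at nominal 10% given 3 events.

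**The case against.** The strongest reply is that little depends on this. The trial is exploratory, the adverse-event analysis is mainly descriptive with a test only where applicable, and no safety conclusion is tied to a p-value. All of that stands and sets the weight of the point. It does not explain why one sentence asks for the exact test and the other does not.

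Four stronger readings are tempting, and the documents do not support them.

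- *Neither test holds its level.* The exact test never exceeds its level; it is conservative. The ordinary test's unconditional excess is small and disappears for rare events.
- *Both tests are applied to the same 16 v 16 tables.* The analysis sets are defined differently. Read literally, the safety set holds only patients given the investigational therapy, which would leave no control column. The text nevertheless compares the two groups, so a two-arm comparison is evidently intended, but 16 v 16 remains an assumption.
- *The trial tests safety at 10%.* That level is given for the primary endpoint only.
- *An unconditional exact test is required.* The conditional exact test is valid and standard, so preferring Boschloo or Barnard is a choice and does not correct an error. The two can also differ: for 0 v 4, Boschloo gives p = 0.0502 and the Pearson-ordered Barnard test 0.0448.

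**Conclusion.** The inconsistency is real and minor. The article prescribes two different tests for overlapping, sparse two-arm proportions without a reason. On the assumption of about 16 v 16 in both analyses, the choice of test changes significance in 26 of 289 tables at an assumed 5% level and in 28 at 10%, always towards significance under the ordinary test. These are counts of possible tables, not the probability that the trial will meet one. The ordinary test's worst-case excess over its level is 0.8 percentage points at 5% and 1.0 at 10%. The exact test needs no repair on grounds of validity. The size pattern is similar for 15 v 15 and 15 v 16.

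**What to change.** Change the adverse-event sentence so that specific adverse events, perioperative morbidity and perioperative mortality are all compared with the same exact test, named in advance. Report each with the risk difference and an exact confidence interval. The exact chi-square already planned for morbidity and mortality is sufficient.

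One named unconditional exact test, for example Boschloo, is an optional and more powerful alternative. At 16 v 16 such tests have a maximum size of 4.1–4.5% at nominal 5% and 8.3–8.6% at nominal 10%. For morbidity of 45.9% (cited in the Discussion) against an assumed 20%, power at 10% rises from 32% with the conditional test to 41–44%. If this route is taken, a single test must be named, because the candidates can disagree.

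The cost is a change of wording, with no added patients or data. The downside is that adverse-event p-values become larger than with the ordinary chi-square. With the planned exact test, 0 v 4 gives 0.101, and a split from zero first reaches 5% at 0 v 5 (2 × C(16,5) / C(32,5) = 2 × 4368 / 201376 = 0.043).

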## Discussion

POPF is the most relevant PD-associated complication. A recently published ISGPS recommended classification system emphasized a soft pancreatic textur and a small pancreatic duct ≤ 3 mm as the most relevant risk factors for developing POPF [22]. Accordingly, patients at very high-risk of POPF are labeled as ISGPS-D. In these patients, an overall morbidity of 45.9% and in-hospital mortality of 4.1% was reported [23]. These results illustrate that the surgical outcome after PD can have influence on the onlogical long-term outcome. Mackay et al. reported that only one third of patients receive their indicated adjuvant treatment after pancreatic surgery, mostly due operation-associated complications [24]. A previous study had even demonstraded that 67.4% patients with serious POPF-associated complications never delivered adjuvant chemotherapy [25]. These facts leaving a little room for improvement through prophylactic TP. However, a recently systematic review and meta-analysis found no superiority of TP in terms of reduction in short-term mortality and major morbidity compared to high-risk PD [26]. Pancreoprivic diabetes inherently resulting from TP represents the most severe form of diabetes due to complete insulin and glucagon deficiency and consecutively is often associated with severe metabolic lability and frequent hypoglycemia. Furthermore, there is increasing evidence that the quality of metabolic control is strongly correlated with oncologic outcome [27]. Therefore, the results of the recently published PAN-IT trial encourage that total pancreatectomy with simultaneous IAT may become the standard treatment for malignant diseases in candidates for PD, when a high risk of POPF is predicted [28].

The above described product used in this pilot study is already used in standard care at the study site in both allogeneic and autologous settings. The relevant risks relate to the implantation procedure and oncological aspects. Procedure-associated complications are limited to the risk of portal vein thrombosis due to intraportal infusion of islet cells. This risk can be controlled by performing continuous portal pressure measurement during infusion as well as by systemic anticoagulation. Overall, this risk is considered to be low.

A potential risk of IAT in patients with pancreatic malignancy is the transfer of dysplastic cells and induction of liver metastases by intraportal transplantation. During the islet isolation process, endocrine cellular portions of the pancreas are enriched, but complete elimination of ductal cells cannot be guaranteed. However, studies from Balzano *et al.* demonstrated that the oncologic outcome after IAT in patients with malignant disease is not worse compared with patients treated according to standard protocols [10,29]. Moreover, in the case of standard pancreatic head resection, pancreatic parenchyma with potentially dysplastic cells remains in situ. Therefore, the purification and thus significant reduction of exocrine/ductal fractions performed in the course of islet isolation and transplantation can be considered equivalent from an oncological point of view with regard to the amount of potentially malignant cells remaining in situ.

The XANDTX pilot trial will aim to provide feasibility and safety data that will generated a hypothesis and basis for a subsequent confirmatory controlled study that has the potential to provide practice changing data.

## Abbreviations

AMG: Arzneimittelgesetz (German Medicinal Products Act)
BMI: body mass index
CRF: case report form
CVC: central venous catheter
ECG: electrocardiogram
eCRF: electronic case report form
FRS: fistula risk score
IAT: islet autotransplantation
GCP: good clinical practice
PD: pancreatoduodenectomy/pancreaticoduodenectomy
PPPD: pylorus-preserving pancreaticoduodenectomy
POPF: postoperative pancreatic fistula
QoL: quality of life
TMF: trial master file
TP: total pancreatectomy.
